**SYNOPSIS**

| **Study Title** | Ultrasound-assisted carbon nanoparticle suspension mapping versus dual-tracer-guided sentinel lymph node biopsy in patients with early breast cancer (UltraCars): a prospective, randomized, controlled, phase 3 trial |
| --- | --- |
| **Clinical Phase** | Phase III |
| **Centers in which trial will be carried out** | Guangdong Provincial People's Hospital, Guangdong Academy of Medical Sciences (Guangzhou, China). |
| **Clinical Research Ethics Committees which have approved the study** | This study was approved by the Research Ethics Committee (No. GDREC2019610H) |
| **Good Clinical Practice (GCP) Study Monitors** | [name]: [contact]  [name]: [contact]  [name]: [contact]  [name]: [contact] |
| **Objectives** | **Principal objective:**  To compare the identification rate of sentinel lymph nodes (SLNs) using an ultrasound-assisted carbon nanoparticle suspension mapping versus dual-tracer-guided sentinel lymph node biopsy in patients with early breast cancer, defined as the number of patients whose SLNs were detected divided by the total number of patients included.  **Secondary objectives:**   - Median number of SLNs collected; - The metastatic rate of SLNs, defined as the number of patients who have at least one positive SLN divided by the number of patients whose SLNs were identified; - Operative duration, defined as the time from skin incision to resection of the SLN specimens; - Intraoperative or postoperative complications.   **Exploratory objectives:**  The identification rate of SLNs in patients after neoadjuvant therapy. |
| **Study design** | This study is a single-centre, open-label, randomized controlled, non-inferiority, phase 3 trial. Patients will be randomly assigned (1:1) using a permuted block randomization scheme to receive either ultrasound-assisted CNS (UC group) or CNS plus ICG dual-tracer-guided (GC group) SLN mapping.   - UC group: Intraoperative ultrasound-assisted CNS will be used for SLN mapping. - GC group: CNS plus ICG dual-tracer-guided SLN mapping.   All removed lymph nodes will be sent for intraoperative frozen section analysis. Axillary lymph node dissection will be undertaken according to the pathologic findings of the SLNs and the current international guidelines. |
| **Inclusion criteria** | 1. The patient must be female and 18 years of age or older.  2. Resectable invasive adenocarcinoma of the breast, histologically confirmed by core or open biopsy.  3. Ductal carcinoma in situ histologically confirmed by core or open biopsy and scheduled for mastectomy.  4. The breast cancer must be preoperative clinical Tis, T1, T2, T3, M0.  5. Without clinical or radiological nodal involvement (cN0): no positive ipsilateral axillary lymph nodes; no prior removal of ipsilateral axillary lymph nodes; no suspicious palpable nodes in the contralateral axilla or palpable supraclavicular or infraclavicular nodes, unless proven nonmalignant by biopsy.  6. With clinical positive lymph nodes (cN1) (including any abnormal or enlarged clinically palpable lymph nodes or core biopsy/surgical biopsy/FNA evidence of malignant cell within any lymph nodes) that was downstaged to cN0 following neoadjuvant therapy.  7. The patient must have an ECOG performance status of Grade 0-1.  8. The patient must provide written informed consent before participating in the study. |
| **Exclusion criteria** | 1. The breast has ulceration, erythema, infiltration of the skin or underlying chest wall (complete fixation), peau d'orange, or skin edema of any magnitude. Tethering or dimpling of the skin and nipple inversion is allowed.  2. The patient has a known hypersensitivity to tracers planned for use during SLNB.  3. Other prior breast malignancy except for lobular carcinoma in situ.  4. The patient has had prior breast implants.  5. The patient has had prior breast reduction surgery.  6. The patient has had other prior surgery in the upper, outer quadrant, areola, or axilla on the side of the affected breast.  7. The patient has a positive pregnancy test or is lactating.  8. The patient has participated in another investigational drug study during the 30 days prior to signing informed consent. |
| **Study population and total number of patients** | PASS 2019 software was used to calculate the required sample size. The non-inferiority (one-sided) hypothesis is adopted, which assumed an SLN identification rate of 96% for each group, and a non-inferiority margin (∆) of 6% to secure an identification rate above 90% (one-sided test significance level (α) =0.05). A sample size of 264 patients was required to give a power of 80% to reject the null hypothesis that the identification rate in the UC group was inferior to that of the GC group by more than a 6% non-inferiority margin (with a 5% probability of type I error). Anticipating a 10% dropout rate, at least 294 patients will need to be recruited. |
| **Timing and planned completion date** | **Initiation of inclusion:** December 2019  **Completion of inclusion:** May 2021  **Final analysis:** Third quarter 2021 |

**STUDY DESIGN**

This study is a single-centre, open-label, randomized controlled, non-inferiority, phase 3 trial. The patients will be randomly assigned (1:1) using a permuted block randomization scheme to receive either ultrasound-assisted CNS (UC group) or CNS plus ICG dual-tracer-guided (GC group) SLN mapping.

UC group=ultrasound-assisted CNS for SLN mapping. GC group=dual-tracer method using CNS plus ICG for SLN mapping. DCIS=ductal carcinoma in situ. ALND=axillary lymph node dissection. CNS=carbon nanoparticle suspension. ICG=indocyanine green.

**[name]**

**Signature: _____________________________________ Date: ___________**

**1. INTRODUCTION**

**1.1 Background**

**1.1.1 Lymphatic Mapping and Sentinel Lymph Node Biopsy**

The current treatment of breast cancer involves various combinations of multiple treatment modalities including surgery, radiation and systemic therapy. Traditionally, regional lymph node status was thought to be the most important determinant of the required extent of surgery and the need for systemic and radiation therapy^1^. Axillary lymph node dissection (ALND) is, however, associated with significant morbidity (lymphedema, pain and decreased range of motion postoperatively). Therefore, sentinel lymph node biopsy (SLNB) has become the standard of care in clinically node-negative (cN0) early breast cancer (EBC) due to its low false-negative rates (FNRs), without impairing local control or survival^2,3^. This less extensive staging procedure has allowed safe omission of ALND in approximately 60% of patients with no pathological evidence of disease in the excised sentinel lymph nodes (SLNs)^4^.

Since their first descriptions during breast cancer by Krag in 1993^5^ and Giuliano in 1994^6^, intraoperative lymphatic mapping and SLNB have become standard-of-care technologies widely utilized in the surgical staging and treatment of breast cancer. The utilization of SLNB for breast cancer has resulted in a reduction in the short-term complications and long-term morbidities, including lymphedema, associated with ALND^7-10^. Additionally, the utilization of SLNB has allowed for the avoidance of ALND in cases of early-stage breast cancer with limited SLN involvement in both cases of breast-conserving surgery and mastectomy^11,12^.

An ideal lymph node mapping agent for SLNB should exhibit rapid clearance from the injection site, rapid uptake and high retention within the first draining lymph nodes, and low uptake by subsequent, higher echelon lymph nodes. The ideal lymph node mapping agent should also have biochemical purity, molecular size uniformity, and a high level of biological and radiation safety. Specifically, a radiopharmaceutical lymph node mapping agent should possess characteristics allowing for convenient, rapid, and stable ^99m^Tc labeling.

At present, gold standard lymphatic mapping uses a combination of blue dye (BD; patent blue, methylene blue, or isosulfan blue) and radioactive colloid^13-16^. This dual tracer approach facilitates high sensitivity and low FNR^14^. However, BD can cause allergic reactions in 1.8% of patients, among which approximately 23% are type I hypersensitivity and 69% are type IV skin reactions^17^. Additionally, BD can cause semipermanent skin staining/tattooing, which may or may not fade after several months^18^, and the technique may fail to accurately identify all sentinel nodes when used in isolation^19^. Radioactive colloids expose both the patient and staff to radiation^20,21^, require a constant supply due to their short shelf-life (but there are limited numbers of nuclear reactors capable of making medical-grade isotopes)^22^, may not be widely available to all hospitals, mandate special licensing and hospital infrastructure for safe use and disposal as per the Ionizing Radiation Medical Exposure Regulations^23^, and, when used in isolation, fail to give a visual cue for nodal stations. The limitations of both dye and radioisotope (RI) mapping have led to the development of new contrast agents for SLNB, such as magnetic^24,25^ and fluorescence imaging approaches^26-36^.

In the era of minimally invasive surgery for breast cancer, the good benefits of neoadjuvant chemotherapy (NCT) have encouraged surgeons to adopt more conservative surgical approaches to reduce the incidence of complications and adverse reactions further. After NCT, approximately 21.1% (10.1-74.2%) of patients are able to achieve a pathological complete response (pCR)^37^, among which the axillary pCR rate is between 23-74%^38,39^. The FNR of SLNB after NCT in breast cancer has been reported to be 8-14.2%^37^. Currently, the American Society of Breast Surgeons recommends that SLNB FNR be controlled at approximately 5%^40^, which suggests that the method should be improved to reduce the FNR. The current NCCN guidelines suggest that the goals of neoadjuvant therapy include reducing the possibility of axillary breast cancer in the retained axillary lymph nodes, but the precise resection of metastatic axillary lymph nodes is an important issue in axillary surgery. For axillary metastatic lymph nodes confirmed by pathological biopsy before neoadjuvant therapy, a clip can be inserted to locate them after NCT, which allows them to be completely removed by SLNB, which is the primary concept of targeted axillary resection (TAD)^41^. The results of the ACOSOG Z1071 clinical trial showed that cases with clip-labeled biopsy greater than or equal to 3 SLNs (double tracer) were associated with a lower FNR (clip-labeled FNR: 6.8%; unlabeled FNR: 13%)^42^. Before NCT, the lymph nodes were labeled with radioactive iodine 125 particles. After NCT, targeted surgery was performed to control the FNR at 7%^43^. TAD with radioactive iodine 125 particles was performed at the MD Anderson Center to further reduce the FNR to 2%^44^. In a clinical trial evaluating the feasibility of intraoperative ultrasound-guided removal of clip-labeled SLNs, 44 (96%) of 46 cases were successful in the removal of clip-labeled axillary metastatic lymph nodes. The overall FNR was 4.1% (95% CI 0.1-21.1%)^45^.

**1.1.2 Alternative Methods for SLN Mapping**

Contrast-enhanced ultrasound (CEUS) using microbubbles is a new technique that potentially allows SLNB to be performed outside the operating theatre. Three studies followed the same protocol and showed an SLN identification rate between 87.7% and 89%^46-48^. The most recent and largest cohort study^48^ involving 347 patients was the only study that attempted to accurately calculate the sensitivity of the technique, for which they identified 22 false-negative results, providing a sensitivity of only 61%. Further refinement of this system with improved sensitivity could provide an alternative to surgical sentinel lymph node biopsy.

Superparamagnetic iron oxide (SPIO) has been used as an MRI contrast agent for preoperative assessment of sentinel lymph nodes with better results than other imaging modalities such as PET^49,50^. The study by Shiozawa and colleagues^51^ considered the performance of SLNB in breast cancer patients using SPIO and a handheld magnetometer. This study was limited by its small size and the comparison of SPIO to blue dye only as opposed to a dual technique but it showed SPIO to be more sensitive than blue dye, albeit significantly below the accepted sensitivity for the dual technique. However, even in this study, the FNR of the magnetic technique (8%) was twice that of the standard technique (4%) based on the 25 patients who were node-positive after sentinel lymph node biopsy (no compulsory axillary node clearance). Additionally, the authors identified a discordance rate of 6.9% for nodes identified by the two techniques. This finding suggests that the magnetic technique does not always identify the same nodes as the dual technique, which might be a limitation because it leads to false-negative staging. However, this situation could represent differences in the standard techniques used by the centers within this trial.

The potential benefits of SPIOs include their half-life of several years, which enables them to be shipped to remote locations worldwide. They do not need special handling procedures, which eliminates the issues of scheduling with a nuclear medicine department and safe waste disposal. SPIOs are not believed to be toxic or dangerous in clinical use. SPIO can be injected intravenously or interstitially, and they are taken up by macrophages in the mononuclear phagocyte system of the liver, spleen, lymphatic system and bone marrow and broken down to be distributed across iron stores in the body^52^. Their main drawback is the need to remove metal retractors from the wound when using the magnetometer to take readings during surgery. Further assessment of this technique is warranted in larger studies against the dual technique.

There is a growing body of literature supporting the role of indocyanine green (ICG) dye in lymphatic mapping. ICG is a fluorescent dye that can be detected using near infrared cameras. The use of ICG in conjunction with a near infrared camera offers many potential advantages over the use of other techniques, including the ability to inject the material while the patient is under anesthesia in the operating room, the ability to directly visualize lymphatic flow using near infrared imaging, and no special requirement for material handlings. ICG is approved by FDA for vascular fluorescence and liver function studies in humans. ICG is a heptamethine indocyanine with moderate optical properties which that emits 800 nm. There are many uses for ICG during image-guided surgery. After intravenous injection, it can be used for near-infrared (NIR) angiography of blood vessels, identification of the extrahepatic bile ducts, and identification of liver metastases. After subcutaneous injection, ICG has been reported by numerous authors to be safely used for SLN mapping^53-57^ and assessing lymphatic function^58^. ICG has been used for the last 50 years as a visible dye (green for ICG), and there is an unprecedented body of clinical data regarding its safety when used at millimolar concentrations^58^. The use of ICG for lymphatic mapping in breast cancer patients has been demonstrated to be safe in numerous human studies^59-63^. A study from Europe demonstrated high concordance between the number of nodes identified with ICG and ^99m^Tc-labeled radiotracers^63^.

**1.1.3 Carbon Nanoparticle Suspensions (CNS)**

Another promising sentinel lymph node tracer is carbon nanoparticle suspensions (CNS). With advancements in nanotechnology, CNS could be widely used in surgeries. CNS, which contains particles with a diameter of 150 nm, can easily pass through the lymphatic vessels (diameter, 120–500 nm) but are unable to pass through the blood capillaries (diameter, 20–50 nm). Previous studies have demonstrated the safety of CNS^64^. In recent years, CNS has been used as a lymph node tracer during surgeries for thyroid cancer, gastric cancer, and colorectal cancer^65-67^.

Our previous study showed that CNS is a nonallergic sentinel lymph node tracer that has a good detection rate (99%)^68^. CNS has a large particle diameter, so it has difficulty entering blood vessels. In addition, CNS can readily pass through the lymphatic vessels and ultimately accumulate in the lymph nodes, staining them black for easy recognition. The CNS dye stays in the lymph nodes for an extended time, giving the surgeon a sufficient window for SLN detection. Moreover, CNS does not cause black staining of the surgical area. However, surgeons do need a certain amount of time to practice and master this staining method for sentinel lymph node biopsy.

**1.1.4 Ultrasound-guided Surgery**

ICG and RI are able to provide deep insight into the SLNB location prior to skin incision. However, when the CNS technique is used alone for SLNB, it depends on the surgeon's naked-eye observation and experience, which may prolong the duration of surgery. Therefore, locating black-stained lymph nodes during surgery still requires improvement.

An easily available and feasible method to improve the amount of healthy breast tissue spared while ensuring tumor-free resection margins is intraoperative ultrasonography (US). US-guided surgery enables the surgeon to visualize the tumor during excision. Previous studies have clearly shown the efficacy of US-guided surgery for nonpalpable tumors. Rahusen et al. reported that US-guided surgery, during which an experienced radiologist performed the US, is superior to wire-guided surgery with respect to tumor-free resection margins (89% and 55% of cases, respectively). Snider et al. also showed an excellent rate of tumor-free resection margins using USS (82%) with a smaller volume of healthy breast tissue resection compared to wire-guided surgery (62.2 cm^3^ and 81.1 cm^3^, respectively)^69-74^.

Previous anatomical studies have revealed that the SLNs are neither evenly nor randomly distributed in the axilla but are instead located in predetermined anatomical regions. K.B. Clough et al. found that the SLNs in 86.8% of breast cancer patients were located in the area adjacent to the lateral thoracic tributary of the axillary vein (LTV), extending from the lower border of the axilla to the second intercostobrachial nerve (ICBN), and, more noticeably, 98.2% of SLNs were found in the medial part of the axilla, alongside the LTV, regardless of the site of the primary tumors^75^. These results are consistent with a previous autopsy study in which 87% of axillary SLNs were located between the lateral border of the pectoralis major muscle and the thoracoepigastric vein^76^. Considering the close proximity between the LTV and the lateral border of the pectoralis major muscle^76-68^, the present study used the lateral border of the pectoralis major muscle as a convenient surface landmark for the localization of axillary SLNs.

Ultrasound is a noninvasive method that can not only be used to check whether axillary lymph nodes have metastasized before surgery but can also help to determine the anatomical locations of suspicious lymph nodes. Based on these findings, the following questions have arisen: Can the CNS be used as a tracer for sentinel lymph node biopsy with the help of ultrasound to identify sentinel lymph nodes in the conventional anatomical position? Can ultrasound replace ICG or RI for locating sentinel lymph nodes?

**1.2 Rationale**

The purpose of this prospective, randomized controlled phase 3 trial is to compare the feasibility and diagnostic performance of ultrasound-assisted carbon nanoparticle suspension mapping versus dual-tracer-guided sentinel lymph node biopsy in patients with early breast cancer.

**2. STUDY OBJECTIVES/ENDPOINTS**

**2.1 Principal Objective**

- To compare the identification rate of SLNs by ultrasound-assisted carbon nanoparticle suspension mapping versus dual-tracer-guided sentinel lymph node biopsy in patients with early breast cancer.

**2.2 Secondary Objectives**

- To compare the median number of SLNs collected;
- To compare the metastatic rate of SLNs, defined as the number of patients who have at least one positive SLN divided by the number of patients whose SLNs were identified;
- To compare the operative duration, defined as the time from skin incision to resection of the SLN specimens in patients with at least one SLN detected;
- To compare the intraoperative or postoperative complications.

**2.3 Exploratory Objectives**

- To compare the identification rate of SLNs in patients after neoadjuvant therapy.

**3. PATIENT SELECTION**

Up to 294 evaluable subjects (147 per cohort) will be enrolled in this trial. Evaluable subjects will be randomly assigned (1:1) using a permuted block randomization scheme to receive either ultrasound-assisted CNS (UC group) or CNS plus ICG dual-tracer-guided (GC group) SLN mapping. Determination of the study eligibility will be established by the investigators on the basis of the inclusion and exclusion criteria.

The inclusion/exclusion criteria were designed to ensure that the study subjects have a diagnosis of primary breast cancer and were candidates for surgical intervention as a treatment for breast cancer.

Subjects who meet all of the inclusion criteria and none of the exclusion criteria will be eligible for enrollment in this trial. Written, dated informed consent will be obtained from all subjects before enrollment in the study.

**3.1 Inclusion Criteria**

Patients meeting all of the following inclusion criteria by the end of the screening phase should be considered for admission to the study:

1. The patient must be female and 18 years of age or older.

2. Resectable invasive adenocarcinoma of the breast, confirmed histologically.

3. Ductal carcinoma in situ confirmed by histologically scheduled mastectomy.

4. The patient must have preoperative clinical Tis and T1, T2, T3, M0 breast cancer.

5. Without clinical or radiological nodal involvement (cN0): no positive ipsilateral axillary lymph nodes; no prior removal of ipsilateral axillary lymph nodes; no suspicious palpable nodes in the contralateral axilla or palpable supraclavicular or infraclavicular nodes, unless proven nonmalignant by biopsy.

6. Clinically positive lymph nodes (cN1) (including any abnormal or enlarged clinically palpable lymph nodes or core biopsy/surgical biopsy/FNA evidence of malignant cells within any lymph nodes) were downstaged to cN0 following neoadjuvant therapy.

7. The patient must have an ECOG performance status of Grade 0-1.

8. The patient must provide written informed consent before participating in the study.

**3.2 Exclusion Criteria**

Patients will not be entered into the study if they meet any of the following exclusion criteria:

1. The breast has ulceration, erythema, infiltration of the skin or underlying chest wall (complete fixation), peau d'orange, or skin edema of any magnitude. Tethering or dimpling of the skin or nipple inversion is allowed.

2. The patient has known hypersensitivity to any of the tracers planned for use during SLNB.

3. Other prior breast malignancies except for lobular carcinoma in situ.

4. The patient has had prior breast implants.

5. The patient had prior breast reduction surgery.

6. The patient had other prior surgery in the upper, outer quadrant, areola, or axilla on the same side as the affected breast.

7. The patient had a positive pregnancy test or was lactating.

8. The patient participated in another investigational drug study during the 30 days prior to signing informed consent.

**4. RANDOMIZATION TO THE TREATMENT ARM**

The participating investigators will be responsible for ensuring that each new patient fulfills the study inclusion criteria, is informed appropriately about the study, reads and understands the patient information sheet and dates and signs the informed consent form for participation in the study.

An interactive response system will be used to achieve treatment assignment. A randomization sequence will be created with a 1:1 allocation. Randomization envelopes, numbered with sequential subject IDs, will be prepared by the research office personnel. Each envelope will contain a card identifying the test type assigned to that subject ID. The randomization envelopes will be maintained in a secure fashion in the research office.

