**4.1 Timing of Registration and Randomization to Study**

Eligible patients will sign the informed consent form to agree to participate in the study. The randomization should be completed at least one working day in advance of the planned operation date. No more than 14 days must elapse between the date of treatment randomization and the date of operation. The interval between Day 1 of the last cycle of neoadjuvant chemotherapy and randomization to the study could be no more than 8 weeks (2 months).

The study monitor will notify the investigator by electronic mail, within a period of one working day, of the patient study number and treatment arm to which she has been randomized. This study is unmasked, and all patients, investigators and surgeons will be aware of the study group assignment.

The administrative coordinator of the study registered all selected patients before beginning the operation. Patients who were not registered before the operation will not be permitted to participate in the study.

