**5. PATIENT TREATMENT**

**5.1 Preoperation Chemotherapy**

Standard neoadjuvant therapy before randomization will be performed according to the NCCN guidelines and clinical practice.

Evaluation of neoadjuvant chemotherapy (every 2 cycles):

- Breast and axillary ultrasound (every 2 cycles)
- Mammogram (first plus one before surgery)
- Breast MRI (first plus one before surgery)

Quality control of SLNB after neoadjuvant therapy entails removal of the clip-containing node and at least 3 lymph nodes. Intraoperative radiography will be used to identify the clipped node.

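### Section 4 gives two assignment routes without saying which one operates, so concealment is not secured; separately, allocation is not stratified by neoadjuvant therapy, which mainly costs precision

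*Protocol*

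**What the plan says.** **Assignment route.** Protocol Section 4 opens its description with "An interactive response system will be used to achieve treatment assignment". The same paragraph continues "Randomization envelopes, numbered with sequential subject IDs, will be prepared by the research office personnel", then "Each envelope will contain a card identifying the test type assigned to that subject ID" and "The randomization envelopes will be maintained in a secure fashion in the research office". Section 4.1 adds how the result is passed on: "The study monitor will notify the investigator by electronic mail, within a period of one working day, of the patient study number and treatment arm". Section 4.2 speaks of a randomization system. Section 6.1 gives no further detail and points to Section 4.

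**Setting.** The Study Design section describes one centre, open label, 1:1 allocation in permuted blocks. Section 4.1 says that patients, investigators and surgeons all know the arm.

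**Neoadjuvant therapy.** No stratification factor is named anywhere. Section 2.3 sets one exploratory objective: "To compare the identification rate of SLNs in patients after neoadjuvant therapy". Section 5.1 requires, after neoadjuvant therapy, "removal of the clip-containing node and at least 3 lymph nodes". Section 6.3.3 compares secondary endpoints with unadjusted chi-squared, Fisher and t-tests.

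**The concern.** An interactive system and a set of pre-filled envelopes are two different sources of the same assignment. They differ in who can see an arm before a patient is committed to the trial. If the system operates, the arm need not exist in readable form until it is requested. If the envelopes operate, every arm is tied in advance to a subject ID. Concealment then depends on sealing, on opening rules and on the order in which IDs are issued, and Section 4 states none of these. Those who enrol also see all past arms. If the next arm could be inferred, the choice of which patient to enter next could depend on it, and that would bias the primary comparison.

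The second issue is separate. Neoadjuvant status is known before randomization and sets a minimum node count, so it bears directly on two secondary endpoints, number of SLNs and operative duration. A chance difference between arms in the share of such patients adds noise to both comparisons, and neither the allocation nor the stated tests remove it.

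**Working it through.** **1. The plan's own figure.** Inputs from Section 6.3.5: 96% identification in each arm, margin 6 points, one-sided alpha 0.05, power 80%.

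- n per arm = (1.645 + 0.842)² × 2 × 0.96 × 0.04 / 0.06² ≈ 132, so 264 in total.
- With 10% dropout: 264 / 0.9 = 293.3, so 294.

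Both stated figures reproduce. Nothing below changes them.

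**2. The two routes side by side.** Sentence one of the Section 4 description assigns by system; the later sentences assign by the card in the envelope for that ID. No text ranks them or calls the envelopes a backup. The e-mail in Section 4.1 comes after randomization and fits either route. Section 4.2 fits the system but does not exclude the envelopes.

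**3. What weak concealment could allow.** The block size is not given, so these are illustrations. In a fixed block of 2b, the share of assignments that are certain, given the block size and all earlier arms, is 1/(b+1). For a block of 4, the six possible orders leave 2, 1, 1, 1, 1 and 2 certain places: 8 of 24, or 33%. Someone who knows only past arms, and always guesses the arm that is behind, does as follows (simulation over 294 patients):

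| Block | Certain if size known | Correct guesses |
|---|---|---|
| 2 | 50% | 75% |
| 4 | 33% | 71% |
| 6 | 25% | 68% |
| 8 | 20% | 66% |
| mixed 4/6/8 | not computed | 68% |

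Chance alone gives 50%.

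**4. Imbalance in neoadjuvant share.** The share s is not in the Protocol and is assumed. With 147 per arm (Section 3), the SD of the arm difference in share is sqrt(2s(1−s)/147).

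| s | SD (points) | P(gap ≥ 10 points) |
|---|---|---|
| 20% | 4.7 | 3.2% |
| 30% | 5.3 | 6.1% |
| 40% | 5.7 | 8.0% |

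Simulation with unstratified blocks of 4 gives a 95th-percentile arm difference of 10, 13, 15 and 17 patients for s = 10%, 20%, 30% and 40%.

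**5. Effect on the primary difference.** Shift = (patient difference / 147) × deficit in identification after neoadjuvant therapy. The deficit is assumed to be 5 to 10 points; the Protocol gives none.

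- Smallest case: 10/147 × 5 = 0.3 points.
- Largest case: 17/147 × 10 = 1.2 points.

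The margin is 6 points.

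**6. Effect within the subgroup.** Unequal numbers inflate the variance by 1/(4pq). A 57:43 split (95th percentile at s = 40%) gives 1/(4 × 0.57 × 0.43) = 1.02. A 67:33 split (s = 10%) gives 1/(4 × 0.67 × 0.33) = 1.13. This is a loss of precision of 2% to 13%, with no bias.

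**The case against.** The strongest reply on concealment is that the envelopes are prepared and kept by the research office, and nothing says that recruiting surgeons can reach them. The two sentences might describe a main route and a backup. Sections 4 and 4.1 already have investigators confirm eligibility and obtain consent, and the arm is reported for a patient who has been randomized. Much of this stands: it makes subversion less likely and shows that the intended order is broadly right. It does not settle which route operates, and no explicit recording step precedes release of the arm.

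On stratification, the reply is that unstratified permuted blocks are a legitimate choice with 294 patients, that the clip and node rule applies to both arms, and that adjusted analyses may sit in a statistical analysis plan not shown here. It is right that the choice is not an error. Stratified allocation is nevertheless a protocol matter, and Section 6.3.3 does fix unadjusted tests.

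A reader might infer four stronger things that the document does not support:

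- **That allocation is in fact predictable.** The figures in step 3 need past arms, and the certain shares also need a fixed and known block size.
- **That leaving the block size unstated is a defect.** It is normally withheld from investigators.
- **That the monitor's e-mail is a third, conflicting mechanism.** It only communicates a completed assignment.
- **That the neoadjuvant subgroup is left unbalanced.** Randomization balances it in expectation, and unequal numbers do not bias a comparison within it.

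**Conclusion.** The point holds in two limited parts. First, Section 4 contains an unresolved conflict between two sources of assignment. In an unmasked single-centre trial with permuted blocks, that leaves concealment unsecured. This rests on the text alone; the size of any resulting bias cannot be derived from the document.

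Second, an evident stratification factor is not used. The likely gain from using it is precision for number of SLNs and operative duration, plus a small gain for the exploratory subgroup. The primary difference is little affected: 0.3 to 1.2 points at a 95th-percentile imbalance, assuming a 10-40% neoadjuvant share and identification 5-10 points lower in those patients. The two parts are independent: stratifying would not make the sequence harder to predict.

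**What to change.** **Concealment.** Name the interactive system in Section 4 as the sole operative route. Delete the envelope text, or define the envelopes as a sealed backup with a rule for when one may be opened. State that the arm is released only after consent and eligibility are recorded.

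**Stratification.** Stratify the allocation by neoadjuvant therapy (yes/no), and amend Section 6.3.3 so that the comparisons of SLN number and operative duration are adjusted for it. For patients already randomized, only the stratified analysis is available.

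**Cost.** A change of wording and a minor reconfiguration of the list. The sample size stays at 264, or 294 with dropout.
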